## Abstract

**Background:**

Phobic anxiety disorders are among the most prevalent psychiatric disorders and are burdensome in terms of loss of quality of life and work productivity. Evidence-based treatments are relatively successful in the majority of patients, especially exposure therapy. However, a substantial subset of patients fails to achieve or stay in remission. Preclinical and genetic research have yielded evidence that the cannabinoid system is involved in the extinction of fear, presumed to underlie the beneficial effects of exposure therapy in phobic disorders. A cannabinoid constituent that may enhance endocannabinoid signaling is cannabidiol (CBD), a non-psychoactive component of cannabis. Hence, the addition of CBD to exposure therapy is expected to strengthen effects of treatment. To determine the added benefit of CBD on exposure therapy, we conduct a randomized controlled trial, in which patients in whom previous treatment as usual has not yielded sufficient response receive either CBD or placebo preceding 8 exposure sessions in a double-blind fashion. A subsidiary aim is to explore which (combination of) clinical, behavioral and genetic profiles of patients are related to treatment response.

**Methods/design:**

This is an 8-week multicenter, randomized, double-blind, placebo-controlled trial. Seventy-two patients with social phobia or panic disorder with agoraphobia with incomplete response to earlier treatment will be included from outpatient clinics in the Netherlands. Patients are randomized to augmentation of exposure therapy with 300 mg CBD or placebo. The study medication is administered orally, 2 h preceding each of the eight 90 min exposure sessions. Measurements will take place at baseline, first administration of medication, every session, mid-treatment, last administration of medication, post-treatment and at 3 and 6 months’ follow-up. The primary outcome measure is the score on the Fear Questionnaire (FQ). In addition, determinants of the expected treatment enhancing effect of CBD will be explored.

**Discussion:**

This is the first trial to investigate whether the addition of CBD to exposure therapy is effective in reducing phobic symptoms in treatment refractory patients with social phobia or panic disorder with agoraphobia.

**Trial registration:**

Netherlands Trial Register NTR5100. Registered 13 March 2015. Protocol version: issue date 17 Jan 2018, protocol amendment number 7.

## Background

Phobic disorders (e.g. social anxiety disorder, panic disorder with agoraphobia) are among the most prevalent disorders according to the World Health Organization’s World Mental Health Survey Initiative [1]. These and other anxiety disorders have major impact on health, individual suffering and societal costs [2]. The estimated societal costs in Europe as a result of anxiety disorders were 74.4 billion Euros in 2010, affecting more than 69 million Europeans [3]. Anxiety disorders often co-occur with other mental health disorders [4, 5], and are associated with an increased risk of suicide [6]. Spontaneous recovery from these disorders is uncommon; if left untreated, phobias typically follow a chronic course, with low remission and high relapse rates [7].

The current evidence-based treatment entails exposure with response prevention therapy, either alone or in combination with serotonin reuptake inhibitors (SSRIs). Exposure therapy is relatively successful, with improvement in up to 60% of patients. However, only 30 to 50% of phobic patients achieves full remission [8]. Likewise, treatment with SSRIs is relatively effective, however, many patients experience relapse after discontinuing SSRI treatment [9, 10], while the effects of successful exposure treatment seem to be more sustainable [11]. Considering the high prevalence of anxiety disorders and the large number of patients for whom the anxiety symptoms remain refractory after (repeated) gold-standard treatments, new approaches to the treatment of anxiety are urgently needed [12, 13]. Preclinical as well as clinical studies have pointed to the relevance of utilizing fear learning paradigms for a deeper understanding of the neurocircuitry and neurochemistry of the fear system involved in anxiety disorders [14]. Specifically, patients with anxiety disorders show stronger fear responses during extinction than comparison subjects [15], and poor fear extinction is predictive of poor outcome in exposure therapy [16].

A potential novel target for the facilitation of fear extinction has been derived from preclinical research. The crucial involvement of the cannabinoid system in fear extinction was first shown by Marsicano et al. [17]. The results show that (genetic or pharmacological) blockage of transmission at the cannabinoid receptor 1 (CB1) inhibits extinction of fear in mice. This is not surprising given the fact the CB1 receptors are richly expressed in memory-related brain areas such as hippocampus and prefrontal cortex, and as such can modulate (fear) memory [18]. In the last 15 years many studies have extended this finding using both animal and human subjects (for reviews see [12] or [19]). Animal research has shown that facilitation of the endocannabinoid system (ECS) enhances extinction, whereas blocking or deletion of CB1 receptors impairs extinction. In healthy human subjects we have demonstrated that genetic variation in a CB1 polymorphism significantly affected extinction learning [20]. Furthermore, the administration of cannabinoids in humans has shown to strengthen extinction and protect against reinstatement of fear [21–23]. In summary, previous research clearly points to the ECS as a promising candidate for extinction enhancement. Until now, studies in humans have mainly investigated the effects of delta-9-tetrahydrocannabinol (THC), which has been shown to decrease physiological measures of fear during extinction [24] and recall [21]. However, THC is not suitable for phobic patients given the diversity of psychoactive effects caused by THC, among which the high that recreational users of cannabis seek.

In the meantime, studies have demonstrated the potential benefit of another important ingredient of cannabis: cannabidiol (CBD, for a review see [25]). CBD interacts with several receptors in the brain including cannabinoid receptors 1 and 2, transient receptor potential vanilloid type 1 (TRVP1) and serotonin 1A (5-HT1A) receptor, and inhibits or in other ways negatively affects the function of the enzyme that degrades endogenously released cannabinoid neurotransmitters (fatty acid amine hydrolase; FAAH [26]). In line with FAAH’s function in degrading anandamide [27], inhibition of FAAH has been shown to increase levels of anandamide. Preclinical research indicates that CBD enhances fear extinction and reconsolidation, and co-administrating CB1 antagonists block such effects suggesting that they are exerted via modulation of the ECS [28, 29]. Extinction of conditioned fear is proposed to underlie the effect of exposure therapy [14]. Hence, the finding that CBD specifically affects (the consolidation of) extinction suggests a potential use of CBD in augmenting the effect of exposure therapy. This leads to the hypothesis that administration of CBD during sessions of exposure therapy is expected to specifically enhance the extinction of pathological fears. The advantage of this application is that CBD needs to be administered occasionally, i.e. preceding exposure sessions only.

We aim to take this previous research to the next level by conducting the first randomized controlled trial with CBD versus 7, administered in a double-blind fashion, for the augmentation of exposure treatment in patients with social phobia or panic disorder with agoraphobia. Also, we aim to specifically target patients who have already received one of the gold-standard treatments without responding sufficiently or having relapsed, because this group needs additional approaches most.

The main study aim is to test whether administration of CBD as an augmentation step in exposure therapy can strengthen treatment outcome in patients with phobic disorders who have previously failed to respond satisfactorily to evidence-based treatment. Clinical measurements are used to investigate whether the effect of CBD on exposure is quicker, stronger, or longer-lasting than regular exposure therapy only. Additionally, there are various exploratory subsidiary aims in this study. First, a fear conditioning and extinction task is applied at baseline. This task has shown enhanced fear responses in patients with anxiety disorders as opposed to healthy comparison subjects [30]. This task also revealed different extinction trajectories, with patients being overrepresented in a poor extinction profile [16]. These profiles have also shown to be sensitive to differences between patients who will benefit from exposure treatment and those who will not. A re-extinction assessment is done after the first medication administration. The aim of this task is to explore a) whether patients with a specific profile can particularly benefit from CBD augmentation during exposure, and b) the acute effects of CBD intake on fear extinction. Second, we aim to explore the interactions between specific genetic variation and CBD administration on treatment effect. We are particularly interested in studying whether variants within the cannabinoid receptor 1 gene are involved in a differential response to CBD augmented exposure therapy, including rs2180619 identified in our previous study in healthy individuals associated with impaired spontaneous extinction of conditioned fear [20]. Additionally, impact of genetic polymorphisms within the FAAH gene [31] and genetic polymorphisms identified as being related to treatment response in anxiety disorders [32] will be explored. Similarly, clinical predictors of treatment response will be assessed to determine which sort of patients might benefit most from this augmented treatment. Lastly, we aim to assess cost-effectiveness of CBD enhancement of exposure treatment.

## Methods

### Study design

The study encompasses a multi-site randomized, double-blind, placebo-controlled fixed dose clinical trial for patients with treatment resistant social phobia or panic disorder with agoraphobia. Either placebo (*N* = 36) or 300 mg cannabidiol (N = 36) will be administered 8 times as an adjunct to 8 weekly 90 min sessions consisting of standardized exposure therapy. The study has been approved by the Medical Ethics Committee of the University Medical Centre Utrecht. Written informed consent will be obtained from all participants. The enrollment of the first participant was on 15 February 2016, recruitment is ongoing at the time of submission. Figure 1 displays a flowchart of the study.

**Fig. 1 Fig1:**
[figure not shown]
Flowchart of the study design. Data is collected both during T0-T6 measurements and therapy sessions, see Table 1 for a complete overview

### Participants

#### Inclusion criteria

Adult patients between 18 and 65 years with a phobic disorder (social phobia or panic disorder with agoraphobia), diagnosed with the Structured Clinical Interview on DSM-IV disorders (SCID; [33])At least one attempt to treat the disorder, according to guidelines, either by means of psychotherapy or with the use of serotonergic antidepressants, has induced insufficient clinically relevant response during or after treatment

#### Exclusion criteria

Co-morbid psychiatric disorders, i.e. current severe major depressive or bipolar disorder, psychosis, dependence on alcohol and drugs, as determined by the SCIDMental deficiency (IQ < 80, as determined by the Nederlandse Leestest voor Volwassenen (NLV; [34]))Autism traits (AQ > 32, as determined by the Autism Spectrum Quotient (AQ; [35]))Inadequate proficiency in Dutch, both verbal and written(A history of) epilepsy, brain damage, cardiac, renal or liver abnormalitiesHistory of allergies to medication (adverse reactions or rash)Use of antipsychotic medicationRegular daytime use of benzodiazepines, since use concomitant to exposure has been shown to hamper the treatment effect [36]Changes in dosing regimen of serotonergic antidepressants shorter than 4 weeks prior to study entry (i.e. use of serotonergic antidepressants at a stable regimen throughout the study is permitted)Use of recreational drugs (among others THC, XTC, cocaine) from 2 months preceding study entryPregnancy or breastfeeding

### Sample size

The CBD and placebo groups will each include 36 patients. The sample size is aimed at detection of a Cohen’s D effect size of 0.6, based on effect sizes found in previous published studies on the augmentation of exposure with d-cycloserine [37]. This sample size has been calculated using G*power version 3.0.10 [38], with a repeated measures design for two groups with two measurements, an envisioned effect size of 0.6 Cohen’s D, error probability of 0.05, power of 0.8 and correlation among repeated measurements of 0.6 based on previous clinical data.

### Recruitment

Patients will be recruited at anxiety outpatient clinics of specialized mental health care centers in the Netherlands (Altrecht, GGZinGeest and UCP). Before including patients in the study, they first undergo an intake interview by an experienced therapist. Eligible patients are informed about the study and are invited to a screening and diagnostic interview (SCID) by the researcher or a trained research assistant to confirm in- and exclusion criteria. Patients receive the information brochure and informed consent form if they are eligible and interested in participating. Informed consent is obtained by the researcher or a trained research assistant before the start of the baseline assessment. Additionally, participants can opt to consent to the use of their genetic material in larger international databases.

### Randomization and blinding

The randomization (CBD or placebo) is conducted by an independent statistician using a computer algorithm, stratifying for study location and diagnosis (panic disorder with agoraphobia or social phobia). Patients are allocated to one of the medication groups after baseline measurements according to the order of patients in the stratum. Investigators, research assistants, therapists and participants will be blinded with respect to randomization. The capsules containing the different medications are identical in appearance except for filling which is either CBD or lactose (placebo). An independent data manager can break the randomization code in case of pregnancy, allergic reactions or any severe inexplicable symptoms. Apart from these circumstances, unblinding will not be done until after the last patient has completed the last follow up measurement.

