### Assessments

Response to treatment will be assessed at baseline (T0), at mid-treatment (T2), post-treatment (T4) and at 3 and 6 months’ follow-up (T5 and T6 respectively). During treatment, a short assessment is done at each therapy session. Table 1 provides an overview of the measures that are used at each time point. The primary endpoint of this study is the clinical outcome post-treatment (at assessment T4). The other measurements are aimed at the time course of the effect. The mid-treatment and per session assessments are specifically aimed at examining the possibility of a quicker and/or stronger effect of exposure with CBD as opposed to placebo, whereas the follow up measurements allow evaluation of potential long term beneficial effects of CBD. Furthermore, preceding the first and last treatment session with medication administration (T1 and T3 respectively) several secondary measures will be used to study the mechanism underlying acute effects of CBD. Also, blood samples from these assessments will be used to determine CBD plasma levels.

**Table 1 Tab1:** Overview of assessments

Measure	Assessment	T0	T1	T2	T3	T4	T5	T6	Treat-ments
SCID	Diagnosis	x							
General patient characteristics	Demographic information	x							
Clinical background	Therapy history	x							
CTQ	Childhood trauma	x							
AQ	Autism quotient	x							
FQ	Presence and severity phobic symptoms	x		x		x	x	x	x
BAI	Anxiety severity	x		x		x	x	x	x
CGI	Clinical global impression								x
SUDS	Degree of habituation and extinction								x
BDI	Depression	x		x		x	x	x	
BSQ	Somatic symptoms	x		x		x	x	x	
EQ5D	Quality of life	x		x		x	x	x	
Tic-P	Loss of work and productivity plus health care costs	x		x		x	x	x	
SPAI	Social phobia and anxiety severity	x		x		x	x	x	
LSAS	Social anxiety severity (SOC PHOB)	x		x		x	x	x	
PDSS	Panic disorder severity (PD + AGO)	x		x		x	x	x	
MI	Mobility inventory (PD + AGO)	x		x		x	x	x	
ACQ	Agoraphobia severity (PD + AGO)	x		x		x	x	x	
Fear conditioning task	Acquisition and extinction of fear learning	x	x		x				
Blood	CBD level, DNA, epigenetics		x		x				

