### Statistical analysis

#### Treatment augmentation

Data concerning the primary and secondary outcome measures will be analyzed by comparing the scores on the measurement scales using mixed modeling, with medication (CBD vs. placebo) and time (time points: baseline, mid-treatment, post-treatment and follow-ups). Analyses are conducted according to the intention-to-treat principle, i.e. all patients who have completed the baseline assessment are included in the analyses. Furthermore, also a ‘completers only’ analysis will be done including just the participants who have completed the treatment and participated in all measurements (T0-T6).

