#### Patient profiling

To determine which patient characteristics may predict additional benefit of CBD augmentation, explorative multilevel analyses with treatment success as dependent variable will be performed, with the following independent variables (among others); medication (CBD or placebo), diagnosis (panic disorder with agoraphobia or social phobia), fear learning (response during extinction, and reduction of fear from acquisition to extinction), cannabinoid system genetics (using a candidate gene approach focused on CNR1 and FAAH), prior treatment history (failed CBT, SSRI, or both), clinical state at baseline and demographic variables (gender, age).

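### Allocation is stratified by study location and diagnosis, but the stated mixed model names only medication and time; adding the strata with their time interactions is a cheap, modest gain

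*Protocol article*

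**What the plan says.** All references are to the protocol article.

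- **Randomization and blinding:** allocation is made "stratifying for study location and diagnosis (panic disorder with agoraphobia or social phobia", and patients are assigned "according to the order of patients in the stratum". Blocks or another balancing device are not mentioned.
- **Recruitment:** three centres are named, "Altrecht, GGZinGeest and UCP". If each is a location, there are 3 × 2 = 6 strata.
- **Treatment augmentation:** primary and secondary outcomes are analysed "using mixed modeling, with medication (CBD vs. placebo) and time (time points: baseline, mid-treatment, post-treatment and follow-ups". Baseline is therefore one of the modelled time points. Neither stratification factor is named, and the text does not say which term is the primary test.
- **Assessments:** the primary endpoint is the outcome at T4.
- **Patient profiling:** diagnosis is listed as a model term ("diagnosis (panic disorder with agoraphobia or social phobia), fear learning"), but only for the exploratory analyses.

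**The concern.** The usual rule is to analyse as one randomises. Balancing the arms on a factor removes that factor's contribution from the true variability of the treatment difference. A model without the factor still counts that contribution as residual noise, so its standard error is larger than it should be.

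Diagnosis is a credible predictor here. By the Primary outcome section, the FQ total sums agoraphobia, social and blood-injury items, five of each. By the Intervention section, the two diagnoses follow different exposure protocols.

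What is at stake is efficiency in a trial of 72 patients planned at 80% power, with no dropout allowance given under Sample size. Both factors are known for every patient before allocation.

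**Working it through.** **Inputs from the article (Sample size):** 36 per arm, d = 0.6, alpha 0.05, power 0.80, correlation 0.6, two groups, two measurements. **Assumed:** the share q of the variance of the tested quantity that the strata explain, and whether allocation is blocked.

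**1. The stated sample size.** For a between-group test averaged over m = 2 measurements, f = d/2 = 0.3 and λ = f²·N·m / (1 + (m − 1)ρ) = 0.09 × 72 × 2 / 1.6 = 8.1. With 1 and 70 degrees of freedom, power is 0.801, and 72 is the smallest even N that reaches 0.80. The figure is reproduced.

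This does not identify the planned test. A comparison of change scores with a 0.6 SD difference has variance 2(1 − 0.6) = 0.8 and λ = 0.6² × 36 / (2 × 0.8) = 8.1, again on 70 degrees of freedom. At ρ = 0.6 the two calculations coincide.

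**2. Effect of omitting balanced strata (normal approximation).**

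- Standard error ratio = 1/√(1 − q)
- Type I error = 2[1 − Φ(1.96/√(1 − q))]
- Power without strata = Φ(0.8416/√(1 − q))
- Power with strata = Φ(2.8016/√(1 − q) − 1.96)

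Here 0.8416 is the normal quantile for 0.80, and 2.8016 = 1.96 + 0.8416.

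| q (assumed) | SE ratio | Type I error | Power without strata | Power with strata |
|---|---|---|---|---|
| 0 | 1.00 | 0.050 | 0.800 | 0.800 |
| 0.05 | 1.03 | 0.044 | 0.806 | 0.820 |
| 0.10 | 1.05 | 0.039 | 0.813 | 0.840 |
| 0.20 | 1.12 | 0.028 | 0.827 | 0.879 |

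The losses are 1.4, 2.7 and 5.2 points (the last is 5.3 before rounding).

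**3. Do the conditions matter?** Null simulations used 72 patients, six strata, correlation 0.6 and 4,000 runs per scenario (Monte Carlo error about 0.0034), with the strata left out of the model:

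| Scenario | Test | Rejection rate |
|---|---|---|
| Blocks of 4; constant stratum shift, 20% of each score's variance | T4 score | 0.031 |
| same | mean of baseline and T4 | 0.025 |
| same | change from baseline | 0.050 |
| same | T4 adjusted for baseline | 0.049 |
| Same shift, no blocks | T4 score | 0.048 |
| same | change from baseline | 0.047 |
| Blocks of 4; strata explain 10% of change | change from baseline | 0.044 |
| Blocks of 4; strata explain 20% of change | change from baseline | 0.032 |

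The averaged score is hit harder because its error variance is (1 + 0.6)/2 = 0.8. A stratum variance of 0.2/0.8 = 0.25 is then 0.25/1.05 = 24% of the total.

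**4. Are main effects enough?** Five-occasion random-intercept models were fitted with and without stratum main effects, 150 fits in each of two settings. The baseline-to-T4 medication-by-time estimates agreed to about 1e-14 and their standard errors to about 2e-6. A constant stratum difference cancels within patients, so only stratum-by-time terms can help that contrast.

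**The case against.** The strongest reply is that the model sentence is a summary. It does not say that medication and time are the only terms, and it gives no random effects or covariance structure. Covariates are commonly left to a full protocol or SAP, neither of which is shown. That stands as a caution: the article names only these two terms, which is less than excluding others. It does not dispose of the point, because the next subsection does list diagnosis as a model term, for exploratory profiling alone. As written, the stated primary model does not follow the stratified design.

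A reader might infer more: that the primary standard error is certainly too large and its confidence interval wrong. The article does not support that, since three conditions are left open:

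- **Balance within strata.** Blocks are not mentioned, and the unblocked simulation showed no conservatism.
- **Prediction.** No figure links location or diagnosis to FQ level or change. The make-up of the FQ makes a diagnosis effect plausible but does not show that change differs, and nothing bears on location.
- **The tested contrast.** Baseline is a modelled time point, so a constant stratum difference drops out of a medication-by-time test at T4.

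The last condition does not remove the problem altogether. The tested term is not named, and strata that predict change still make the change test conservative when allocation is blocked.

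**Conclusion.** The mismatch between the stratified allocation and the stated model is real. Its consequence is conditional and modest. If allocation is balanced within strata and the strata explain 5% to 20% of the variance of the tested quantity, type I error falls to between 0.044 and 0.028, and about 1 to 5 points of power are given away. These shares are assumptions. With shares near zero, or without balancing, there is little or no conservatism. In no case is type I error inflated or the treatment estimate biased: the interval would be somewhat wide, not invalid. This is a free improvement of low to moderate priority.

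**What to change.** - **Primary FQ model and scales given to both diagnoses:** add diagnosis (2 levels) and study location (3 levels, if each named centre is a location) as fixed effects, each with its interaction with time.
- **LSAS, PDSS, MI and ACQ**, each given to one diagnosis: add location and location-by-time only.
- **Also state** which term is the primary test at T4 and whether allocation was balanced within strata, since these decide how much the adjustment matters.

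**Cost.** The main effects take 1 + 2 = 3 parameters. With five occasions the time interactions add (1 + 2) × 4 = 12, but at any one contrast the price is about 3 of 70 patient-level degrees of freedom. If the strata turn out not to predict change, the loss is small. Adjusting for all six cells left the empirical standard error of the change contrast at 0.208 with blocks, and raised it from 0.211 to 0.219 without. A very small centre may need pooling, by a rule fixed in advance. The article reports recruitment as ongoing and keeps the code closed until the last follow-up, so the terms can be specified before unblinding.
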